## **Endpoints**

#### Primary end points

- Pain score with 45 degree active flexion of the knee (VAS) 4 hours postoperatively.

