## **Study Design**

**Type of trial:** Placebo-controlled

**Randomization:** Computer-generated randomized lists, sealed envelopes, block randomization of 10 patients.

**Blinding:** Double-blind

**Participants:** Patients set to undergo knee arthroplasty under general anaesthesia

**Number:** 34(evaluable patients)

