# **METHODOLOGY**

## **General treatment plan and medication dosage**

- An examination is made of whether the patient meets the inclusion and exclusion criteria.
- The trial period is 24 hours with T0 = last suture.
- **Standard pre-medication:**
  - 1 hour before arrival in the operating theatre: Paracetamol 1 g per os.
- **Ultrasound-guided insertion of catheter in the Adductor Canal:**
  - The catheter is inserted under ultrasound guidance under general anesthesia.
- **Treatment A**:
  - Adductor Canal Block via catheter inserted with ultrasound guide, with Ropivacaine 0.75%, bolus 30 ml 0 hours postoperatively, followed by bolus with Ropivacaine 0.75%, 15 ml 6 hours postoperatively. At 6 hours postoperatively an infusion catheter is connected with an infusion of Ropivacaine 0.2%, 9 ml per hour. The pump remains connected until the end of the trial 24 hours postoperatively.
- **Treatment B**:
  - Adductor Canal Block via catheter inserted with ultrasound guide, with placebo, isotonic NaCl, 30 ml bolus 0 hours postoperatively, followed by bolus of NaCl, 15 ml, 6 hours postoperatively. At 6 hours post-operatively an infusion catheter is connected with an infusion of isotonic NaCl, 9 ml per hour. The pump remains connected until the end of the trial 24 hours postoperatively.
- **Standard anaesthesia:**
  - General anaesthesia with Propofol and Remifentanil
  - Rocuron 0.5 mg/kg for intubation, no reversal with neostigmine
  - With a fall in blood pressure, ephedrine is given, alternatively metaoxedrin
  - Fluids as needed
  - 30 minutes before the end of anaesthesia, morphine 0.2 mg/kg is given iv
- **Standard postoperative nausea and pain treatment:**
  - Given postoperatively and for the rest of the 24-hour trials starting T0 + 2 hours:
    - Paracetamol 1 g every 6 hours po.
    - Ibuprofen 400 mg every 6 hour if there are no contraindications.
  - Patient-controlled iv morphine (PCA), bolus 2.0 mg, lockout time 15 minutes. Mixture: Morphine 1 mg/ml.
  - In the first hour postoperatively upon declaration of pronounced pain, fentanyl 0.1 mg may be given iv. The dose may be repeated after 10 minutes.
  - If there is a need for additional morphine in addition to the PCA pump, in the first 2 hours postoperatively, bolus doses of 2.5 mg morphine iv can be given on request.
  - Patients who are in regular opioid therapy preoperatively continue this treatment unchanged during the period of the trial.

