## **Clinical assessments**

- **Patient-controlled morphine consumption**:
  - Number of bolus doses delivered in the period 0-8 hours postoperatively is recorded
  - Number of bolus doses delivered in the period 0-24 hours postoperatively is recorded
- **Pain:**
  - Patients' pain is recorded on a Visual Analogue Scale (VAS) of 100 mm, where 0 = no pain and 100 = worst possible pain. Patients state their own pain intensity.
  - Pain is recorded at rest and in connection with 45 degrees active flexion of the knee.
  - Pain is recorded preoperatively before administration of medication, as well as 1, 2, 4, 6, 8 and 24 hours postoperatively, corresponding to the end of the trial period.
- **Side effects:**
  - Nausea and sedation are recorded on a verbal scale (none, mild, moderate, severe) 1, 2, 4, 6, 8 and 24 hours post-operatively.
  - The number of productive vomiting events (volume estimated over 10 ml) is recorded corresponding to the periods 0-1, 1-2, 2-4, 4-6, 6-8 and 8-24 hours post-operatively by interview with the patient.
  - The patient's use of Zofran (mg) 0-8 and 0-24 hours postoperatively is recorded.

The study extends for each patient from introductory conversation to 24 hours postoperatively. The patient receives the above treatments in accordance with a computer-generated randomized list.

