## **Data processing**

The trial will be completed when 34 evaluable patients are included in the study.

The evaluability of each patient in the statistical analyses will be decided before the code is broken. Only subjects for whom data for pain scores at 45 degrees flexion of the knee 0-8 hours postoperatively is available will be included in the statistical analysis. Excluded patients and missing, unused or false data will be described. Data will be stored and evaluation and statistical analysis will be made by computer, where patient anonymity will be preserved and local data legislation will be observed.

Results will be described with mean values and standard deviation of the mean value, as well as median and inter-quartile values. A 5% level of significance will be used. Binomial data will be analysed with Fisher's exact test and ratio-interval data with the Mann-Whitney test. Multiple analyses will be adjusted with the Bonferroni test. Pain scores will be compared with the AUC calculation. Any change to the statistical plan will be accounted for by publication.

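### The unadjusted Mann-Whitney test fixed for the 4 h flexion VAS is valid, but it leaves recorded baseline pain unused and does not estimate the 20 mm mean difference that sized the trial

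*Protocol*

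**What the plan says.** The primary endpoint is a single time point: "Pain score with 45 degree active flexion of the knee (VAS) 4 hours postoperatively". Data processing chooses tests by type of data: Fisher's exact test for binomial data, and "ratio-interval data with the Mann-Whitney test". A 100 mm VAS falls under the second rule, and no covariate is named.

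For reporting, the same section states: "Results will be described with mean values and standard deviation of the mean value, as well as median and inter-quartile values". These are summaries within each group. It adds "Pain scores will be compared with the AUC calculation", without saying whether that sentence reaches the 4 h primary endpoint.

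Clinical assessments shows that a baseline exists: "Pain is recorded preoperatively before administration of medication, as well as 1, 2, 4, 6, 8 and 24 hours postoperatively", and "Pain is recorded at rest and in connection with 45 degrees active flexion of the knee". Neither the endpoint lists nor Data processing gives the preoperative value a role.

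The General treatment plan also admits chronic opioid users: "Patients who are in regular opioid therapy preoperatively continue this treatment unchanged during the period of the trial". The exclusion criteria bar drug abuse only, and Study Design gives "Computer-generated randomized lists, sealed envelopes, block randomization of 10 patients" with no stratification factor.

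The sample size section assumes a mean of about 75 (SD 20), calls a reduction of 20 clinically relevant, and arrives at 17 patients per group with 5% type 1 and 20% type 2 risk.

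**The concern.** The sample size is built on a difference in means, and the named analysis is a rank test. The Mann-Whitney p-value says whether one arm tends to score lower. It does not say by how many millimetres, or how precisely that is known. With 17 per arm the uncertainty is wide enough for this to matter: a statistically significant result can be compatible both with a trivial effect and with one well above 20 mm, and only an interval shows that.

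The preoperative flexion VAS is the same measurement, in the same patient, under the same movement as the primary endpoint. If the two are correlated, adjustment removes noise at no extra data cost. If adjustment is chosen only after the code is broken, in a trial of 34 patients, it is post hoc and open to challenge.

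**Working it through.** **Inputs from the protocol.** Difference 20 mm, SD 20, alpha 5%, power 80%, 17 per arm (sample size section); scale 0 to 100 (Clinical assessments). The SD is quoted for activity pain over the first 24 h and is applied here to 4 h, as the protocol does.

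**Assumptions.** Two-sided testing (the protocol does not state sidedness); baseline-outcome correlation r from 0 to 0.5; share of regular opioid users 20% to 40%. The protocol gives neither r nor the share.

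**1. Reproduce the plan's figure.** Normal approximation: n per arm = 2 × (1.960 + 0.842)² × (20/20)² = 15.7, so 16 per arm. Two-sample t-test (noncentral t): power 78.1% at 16 per arm and 80.7% at 17. A one-sided normal approximation gives 13 and does not match. The stated 34 is therefore a two-sided t-test on a mean difference.

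**2. Power of the named test.** Mann-Whitney was simulated at 17 per arm with normal data (75 v 55, SD 20). Power is 78.2%, or 78.3% with scores clipped to 0-100 and rounded. A further check gave 78.4%. At 18 per arm it is about 81%. The rank test alone costs about 2 to 3 points against the t-test.

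**3. Power with baseline adjustment.** Residual SD = 20 × √(1 − r²). With k covariates, N = 34 and df = 32 − k, chance covariate imbalance inflates the variance of the treatment effect by (N − 3)/(N − 3 − k), which is 31/30 for k = 1 and 31/29 for k = 2. The noncentrality is 20 / [residual SD × √(2/17 × inflation)]. Example, r = 0.5, k = 1: 20 / (17.32 × 0.3487) = 3.31 on 31 df, power 89%. For k = 2 the second covariate is taken as uninformative, the worst case.

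| r (assumed) | Residual SD | Power, baseline VAS only | Power, second covariate added |
|---|---|---|---|
| 0 | 20.0 | 79% | 78% |
| 0.2 | 19.6 | 81% | 80% |
| 0.3 | 19.1 | 83% | 82% |
| 0.4 | 18.3 | 86% | 85% |
| 0.5 | 17.3 | 89% | 88% |

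A simulation of the fitted models agreed within about half a percentage point.

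**4. What an interval would show.** Unadjusted 95% half-width: 2.037 × 20 × √(2/17) = 14.0 mm. An observed difference of 15 mm would have an interval of about 1 to 29 mm, which is significant but does not settle whether 20 mm was reached. With adjustment at r = 0.5 the half-width is 2.040 × 17.32 × √(2/17 × 31/30) = 12.3 mm.

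**5. Chance imbalance in opioid users.** With independent binomial draws, 17 per arm, the arms differ by 4 or more users in about 13% of trials if 20% are users, 19% if 30%, and 22% if 40%.

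**6. Ceiling.** (100 − 75)/20 = 1.25, so a normal curve with the plan's figures puts about 11% of control scores above 100.

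**The case against.** The strongest reply is that the plan is valid as it stands, and that covariates and effect estimates are commonly left to a statistical analysis plan, which is not at hand. Both statements are true. The absence of covariates would not by itself be a finding. The point rests on what the protocol does fix: a rank test, by data type, for an endpoint sized as a mean difference.

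Three stronger readings are tempting and are not supported.

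- *That the result could not show whether 20 mm was reached or excluded.* Group means and standard deviations are planned, and with 17 per arm a reader can derive the crude difference and its interval. The gap is that the contrast and interval are not named as outputs, and that the p-value belongs to a different quantity.
- *That imbalance in opioid use or baseline pain is likely and the test fails to correct it.* Randomization makes the unadjusted test valid, and its type I error already allows for chance imbalance. The protocol gives no share of opioid users. Under the assumed shares a difference of 4 or more is a real possibility, but not the usual case.
- *That adjustment is worth 10% to 33% more patients for nothing.* This follows from 1/(1 − r²) at r = 0.3 to 0.5, but r is not in the protocol and the factor ignores the cost of estimating covariates. Ignoring that cost gives 84%, 87% and 90% power; counting it gives the lower figures in the table.

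A rank test is also a reasonable choice for a bounded scale with a foreseeable ceiling. That is a good reason to keep it as a sensitivity analysis. It does not explain leaving the baseline unused or the difference unreported.

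**Conclusion.** The concern holds as an efficiency and interpretability point, not as a fault in type I error control. The test does not estimate the 20 mm mean difference on which the trial was sized, and preoperative flexion VAS is recorded and left unused.

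Against about 78% to 79% for Mann-Whitney, baseline adjustment would give 83% to 89% power at 17 per arm for correlations of 0.3 to 0.5. Part of that gain is simply the step from a rank test to a mean-based test (81%). At 0.2 or below, adjustment adds little or nothing over the t-test, and with a second, uninformative covariate it can do slightly worse. The figures assume two-sided testing, normal data and SD 20 at 4 h.

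The case for naming an adjusted difference with its interval does not depend on the correlation. The size of the power gain does. The change is worth making because it is cheap; the trial would not be invalid without it.

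**What to change.** In Data processing, name one primary analysis: an ANCOVA of the 4 h flexion VAS on treatment, with preoperative flexion VAS as covariate. Report the adjusted mean difference with its 95% CI and read it against 20 mm. Keep Mann-Whitney, with the Hodges-Lehmann difference and CI, as a sensitivity analysis. State that the residual check will not switch the primary analysis. Limit the AUC sentence to the secondary AUC endpoints.

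Preoperative regular opioid use (yes/no) may be added as a second covariate, on two conditions: that it is defined, and that it is taken from the CRF or health records before the code is broken. Clinical assessments does not list it, and the protocol does not say what counts as regular.

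Cost: a wording change for the baseline covariate, since the data are already collected; one degree of freedom, or two with opioid use; and a residual check, given the likely ceiling on a 0-100 scale. The opioid covariate also needs a definition and data extraction. No additional patients are needed.

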# **STATISTICAL ANALYSES**

## **Calculation of the number of patients**

Results from previous studies suggest that all patients will have pain postoperatively. Average pain scores (VAS) for activity (45 degree flexion of knee) in the first 24 hours based on previous studies is typically around 75 (SD 20) (8). We assess that a reduction of 20 in the pain score (VAS) will be clinically relevant.

With a type 1 failure risk of 5% and a type 2 failure risk of 20%, a total of 34 patients, i.e. 17 in each group, will be required.

It is planned to include a total of 34 evaluable patients in the measure of main effect. To compensate for drop-outs it is aimed to include 36 patients.

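### The protocol fixes plain Bonferroni without placing the single primary endpoint inside or outside the family; state that the primary is tested alone at 5% and use Holm for the secondary endpoints

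*Protocol*

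**What the plan says.** - **Primary end points** names one variable at one time: VAS pain on 45-degree active knee flexion at 4 hours.
- **Secondary end points** has 11 bullets. Three of them (morphine, vomiting, Zofran) each cover 0-8, 8-24 and 0-24 hours. The rest are four pain, two nausea and two sedation measures.
- **Calculation of the number of patients** uses "type 1 failure risk of 5"% and "a type 2 failure risk of 20"%, a control mean of 75 with SD 20, and a 20-point difference. It concludes "a total of 34 patients, i.e. 17 in each group, will be required". There is no allowance for multiplicity.
- **Data processing** sets a 5% significance level, assigns interval data to the Mann-Whitney test, and then says "Multiple analyses will be adjusted with the Bonferroni test". It gives no number of tests and no list of the analyses covered. The next sentence says that pain scores are compared through the AUC, which is a secondary endpoint.

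**The concern.** The multiplicity sentence and the sample size are not tied together. The sample size gives the full 5% to one test. The Bonferroni sentence does not say that this test lies outside the family, and the AUC sentence makes it a little less clear which pain comparison stands alone. At 17 per group, the number of tests in the family could decide whether a 20 mm difference is declared significant, so the text should not leave room to settle this after the results are known.

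A second question arises even if the primary is exempt. The protocol commits the secondary endpoints to plain Bonferroni. These include morphine use, which heads the hypothesis in the Aim section. A step-down procedure with the same error guarantee would never do worse and can do better.

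**Working it through.** **Inputs** (Calculation of the number of patients): difference 20, SD 20, so the standardised effect is 20/20 = 1; 17 per group; type 1 risk 5%; power 80%. The 36 patients to be enrolled allow for drop-outs, so power is computed on the 34 evaluable. Sidedness is not stated. Two-sided is assumed because it reproduces the plan's figure; one-sided gives 13 per group.

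**Step 1: the plan's own figure.**
- Normal formula: n = 2(1.960 + 0.842)² / 1² = 15.7, so 16 per group.
- Noncentral t: the smallest n with at least 80% power is 17 per group. The stated 34 is reproduced.

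**Step 2: number of comparisons.**
- Secondary: 4 pain + 3 morphine + 2 nausea + 3 vomiting + 3 Zofran + 2 sedation = 17.
- With the primary: 18. Counting bullets instead: 11 + 1 = 12.

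**Step 3: power of the primary test at level 0.05/k.** The noncentrality is 1 × √(17/2) = 2.915, with 32 degrees of freedom for the t-test. The normal approximation is Φ(2.915 − z), where z is the two-sided critical value at 0.05/k. Mann-Whitney power comes from 40,000 simulated trials with normal data, means 75 and 55, SD 20.

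| k | level | normal | t-test | Mann-Whitney |
|---|---|---|---|---|
| 1 (primary exempt) | 0.05 | 83.0% | 80.7% | 78% |
| 12 | 0.00417 | 52.0% | 44.6% | 38% asymptotic, 41% exact |
| 18 | 0.00278 | 47.0% | 39.1% | 33% asymptotic, 36% exact |

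Clipping the VAS to 0-100 and rounding gives 32% at k = 18 by the asymptotic test. The ranges from Mann-Whitney to t-test are therefore 32-39% for k = 18 and 38-45% for k = 12. To regain 80% with the primary inside the family, the trial would need 32 per group (t-test) or about 34 (Mann-Whitney, relative efficiency 0.955) at k = 18, and 30 or about 31 at k = 12.

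**Step 4: secondary endpoints, primary exempt.** 0.05/17 = 0.00294. For an assumed 1 SD effect on normal data, power per test is 39.8% (t-test) or about 33% (asymptotic Mann-Whitney).

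**Step 5: Holm against Bonferroni.** Bonferroni compares all 17 p-values with 0.05/17. Holm compares the smallest with 0.05/17, the next with 0.05/16, then 0.05/15, and so on up to 0.05, stopping at the first failure. Each threshold is at least as large as Bonferroni's, so every Bonferroni rejection is also a Holm rejection, and family-wise error is still held at 5%. In a simulation of 17 correlated secondary endpoints with 1 SD effects, average power per true effect rose from about 33% to between 34% and 44%, depending on how many effects were real.

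**The case against.** **A single primary test is not a multiple analysis.** The protocol names one primary endpoint, sizes the trial on it at 5%, and sets the 5% level before it mentions adjustment. Read this way, the sections agree. This stands. A reader might infer that the protocol contradicts itself, or that the trial really has only 32-39% power. The documents support neither. That range needs two things the protocol never says: that the primary is in the family, and that the family numbers 18.

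**The family can be defined in the analysis plan, which is not shown.** This also stands, so the undefined family alone is only a point for clarification. What the protocol itself fixes is plain Bonferroni.

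**Bonferroni is valid, and Holm changes little.** Partly right. Bonferroni does control family-wise error. Holm takes no account of correlation either, and its first step is the same 0.05/17. The gain is modest, but it comes without loss of error control.

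**The harm to secondary endpoints is hypothetical.** The protocol gives no effect size or SD for them, and normal-data power does not carry over to four-category scales or vomiting counts. This stands: the Step 4 and Step 5 figures are illustrative. Nor would a non-significant secondary result amount to a report of no effect, since the protocol requires means, SDs, medians and quartiles to be described.

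**Could linked periods be dropped instead?** The 0-24 hour total is the sum of the other two periods, so a reader might call it redundant. But a test of the total is not implied by tests of its parts, and lower morphine use is a stated hypothesis. Cutting to 14 tests would raise t-test power at the first step only from 39.8% to 42.5%. The documents give no ground for requiring this.

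**Conclusion.** The point holds in two limited parts.

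1. The protocol should say outright that the primary endpoint is outside the Bonferroni family. With it outside, the 34-patient design keeps about 78-81% power (Mann-Whitney to t-test). With it inside, power would be roughly half the planned 80%: 32-39% for 18 comparisons, 38-45% for 12. These figures assume a two-sided test, normal data, a 20 mm difference, SD 20 and 17 evaluable patients per group.
2. For up to 17 secondary comparisons, plain Bonferroni is needlessly conservative because Holm gives the same protection and never rejects fewer hypotheses. The benefit is small when few effects are real and larger when many are.

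Neither part shows an internal contradiction or makes the sample size wrong under the natural reading.

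**What to change.** In Data processing:

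- State that pain on flexion at 4 hours is the only primary analysis and is tested alone at two-sided 5% without adjustment.
- Name the secondary comparisons that form the family and replace Bonferroni with Holm for them.
- Keep all listed periods in the tested set; none needs to be removed.

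This takes one or two sentences, with no extra patients or data. The only downside is that confidence intervals matching Holm's simultaneous control are less simple to construct than Bonferroni intervals.

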###### **Secondary end points**

- Pain score with 45 degree active flexion of the knee (VAS) 1, 2, 4, 6 and 8 hours postoperatively, given as "area under curve" (AUC) calculation for the period 1-8 hours postoperatively.
- Pain score with 45 degree active flexion of the knee (VAS) 24 hours postoperatively.
- Pain score at rest (VAS) 1, 2, 4, 6 and 8 hours postoperatively, indicated as "area under curve" (AUC) calculation for the period 1-8 hours postoperatively.
- Pain score at rest (VAS) 24 hours postoperatively.
- Total need for morphine in the periods 0-8, 8-24 and 0-24 hours postoperatively, administered as patient controlled pain treatment (bolus 2.5 mg, lockout 10 minutes).
- Degree of nausea 1, 2, 4, 6 and 8 hours postoperatively, calculated as an average value for the period 1-8 hours postoperatively.
- Degree of nausea 24 hours postoperatively.
- Number of vomiting events during the periods 0-8, 8-24 and 0-24 hours postoperatively.
- Consumption of Zofran in the periods 0-8, 8-24 and 0-24 hours postoperatively.
- Degree of sedation 1, 2, 4, 6 and 8 hours postoperatively, calculated as an average value for the period 1-8 hours postoperatively.
- Degree of sedation 24 hours postoperatively.

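### The primary endpoint is the 4 h flexion VAS, but the analysis text compares pain by AUC and the sample size uses a first-24-h average, so the primary comparison is not stated cleanly and its power is not shown

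*Protocol*

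**What the plan says.** Four places in the protocol bear on the main pain comparison.

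- **Endpoints, primary:** a single item, "Pain score with 45 degree active flexion of the knee (VAS) 4 hours postoperatively".
- **Endpoints, secondary:** flexion pain and rest pain over the early period, each summarised as an area under the curve ("AUC) calculation for the period 1-8 hours postoperatively"), and separate single readings at 24 h.
- **Calculation of the number of patients:** the planning figure is "Average pain scores (VAS) for activity (45 degree flexion of knee) in the first 24 hours", put at about 75 (SD 20). With a relevant reduction of 20, type I risk 5% and type II risk 20%, the result is 34 patients, 17 per group. Neither the 4 h score nor the AUC is mentioned.
- **Data processing:** "Binomial data will be analysed with Fisher's exact test and ratio-interval data with the Mann-Whitney test", at a 5% level, with a Bonferroni adjustment for multiple analyses whose family is not defined. Then: "Pain scores will be compared with the AUC calculation". The analysed patients are "Only subjects for whom data for pain scores at 45 degrees flexion of the knee 0-8 hours postoperatively is available". The 4 h score is not mentioned here either.

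**The concern.** Three pain summaries are in use where the confirmatory comparison needs one: a reading at 4 h, an AUC, and an average over the first 24 hours. The only sentence on how pain is compared names the AUC, and the evaluability rule suits an AUC better than a single reading. A patient with a valid 4 h score but a gap elsewhere in 0-8 h could be left out of the primary analysis.

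Two things are at stake. If the text lets either the 4 h score or the AUC serve as the main result, the error rate depends on whether the two are adjusted against each other, which the protocol does not say. And the stated power was worked out for a quantity that is not clearly the declared endpoint, so the reader cannot tell what power the primary comparison has.

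**Working it through.** **1. The plan's own figure.** Inputs from the sample-size section: difference 20, SD 20, so standardised effect 20/20 = 1.0; 5% risk, taken as two-sided because sidedness is not stated; power 80%; equal groups. A two-sample t-test needs 16.7, hence 17 per group and 34 in total, with power 80.7% at 17. A one-sided calculation (normal approximation) gives 13 per group and does not match. The arithmetic is sound.

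**2. Power for the 4 h score.** The protocol gives no SD for that reading, so only a range is possible. Assumptions: difference 20, equal SD in both groups, normal data, two-sided 5%, 17 per group. Mann-Whitney power is by simulation.

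| Assumed SD at 4 h | t-test power | Mann-Whitney power |
|---|---|---|
| 20 | 81% | about 78% |
| 22 | 73% | about 70% |
| 26 | 59% | about 56% |

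Why consider SDs above 20? If SD 20 were the SD of each patient's mean of k readings with common correlation ρ, the single-reading SD would be 20/√((1+(k−1)ρ)/k). With k = 6, which is this trial's own number of postoperative pain readings and not a known feature of the cited study:

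- ρ = 0.8: 20/√(5.0/6) = 21.9, t-test power 73%
- ρ = 0.5: 20/√(3.5/6) = 26.2, t-test power 58%

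If SD 20 already describes a single reading, the first row of the table applies.

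**3. Type I error if either result could be claimed.** Trapezoid weights for readings at 1, 2, 4, 6 and 8 h are 0.5, 1.5, 2, 2, 1 (sum 7, sum of squares 11.5). With equal variances and common correlation ρ (assumed):

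- covariance of the 4 h score with the AUC = 2 + 5ρ
- variance of the AUC = 11.5 + ρ(49 − 11.5) = 11.5 + 37.5ρ
- correlation = (2 + 5ρ)/√(11.5 + 37.5ρ)

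For ρ = 0.4 this is 4/√26.5 = 0.78; for ρ = 0.8 it is 6/√41.5 = 0.93. The bivariate normal probability that at least one test is significant under no effect is:

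| ρ | Each test at 5% | Each test at 2.5% (Bonferroni over the two) |
|---|---|---|
| 0.4 | 7.9% | 4.1% |
| 0.8 | 6.7% | 3.4% |

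So the inflation exists only if the two tests are not adjusted against each other.

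**The case against.** The strongest reply is that the primary comparison can be worked out. The Endpoints section names one variable at one time and ranks AUC as secondary. The Mann-Whitney rule at 5% covers a VAS score. The AUC sentence cannot be meant for all pain scores, because the 24 h scores are single readings with no AUC; it probably describes how the serial 1-8 h scores are summarised. All of this stands. A reader might infer that the protocol never tests its primary endpoint, or has no confirmatory test; the documents do not support that.

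A reader might also infer that type I error is inflated. That ignores both the ranking of endpoints and the Bonferroni sentence. The reply is fair but incomplete: without a defined family, one cannot tell whether the two tests are adjusted together or the primary keeps the full 5%.

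A third tempting reading is that the trial is underpowered. The sample-size wording can equally mean a group mean of single readings taken within 24 hours, in which case SD 20 suits the 4 h score. The lower power figures need SD 20 to belong to a patient-level average, which the text does not say.

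On evaluability, the 0-8 h data contain the 4 h score and the decision is taken before the code is broken, so the rule is not a rival endpoint. It still asks for more than the primary analysis needs. Finally, matching tests to variables is often left to an analysis plan, but here the protocol has itself written an unqualified rule that conflicts with its endpoint list.

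**Conclusion.** The inconsistency is in the text and should be removed; severity is moderate. The intended primary analysis, Mann-Whitney on the 4 h flexion VAS at 5%, can be inferred, but the AUC sentence taken at its word replaces it with a secondary comparison. Under an unadjusted either-or claim, type I error would be about 6.7-7.9% (equal variances, common within-patient correlation 0.8-0.4, normal approximation); under a Bonferroni adjustment covering both tests, 3.4-4.1%. The stated 34 patients reproduce. What is missing is support for SD 20 at 4 h: power for the named test is about 78% if that SD is right and falls to about 56% at an assumed SD of 26. The finding is that power is not shown for the primary endpoint, not that it is too low.

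**What to change.** Before the code is broken, make three edits.

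1. **Data processing, AUC sentence.** Replace with: *The primary comparison is the 4 h flexion VAS, tested once with the Mann-Whitney test at two-sided 5%; AUC(1-8 h) on flexion and at rest are secondary, and the Bonferroni adjustment applies to the secondary endpoints.*
2. **Data processing, evaluability.** Base inclusion in the primary analysis on an available 4 h flexion score.
3. **Calculation of the number of patients.** State that SD 20 is assumed for the 4 h score, and give Mann-Whitney power at 17 per group: about 78% at SD 20, 70% at SD 22 and 56% at SD 26 (t-test 81%, 73% and 59%).

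The cost is a few sentences and a slightly less favourable stated power, since the named test falls just under 80% even at SD 20. No extra patients are needed.
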